#### Testing of the new demarcation formula analysis

The same iterative process will be used as described in section [2.1.5.2](#). in the first half of the dataset (training set), to improve the original demarcation formula. This will be validated in the second half of the dataset (validation set or testing set) using the same analyses as in the validation of the original demarcation formula:

- Differences in Lybrido-effect and Lybridos-effect between groups will be analyzed with two-way mixed design ANOVA with 2 within subjects effect variables (Lybrido-effect *versus* Lybridos-effect) x 2 between subjects group variables (Low Sexual Attention versus High Sexual Attention. The dependent variables are the effect variables Lybrido-effect and Lybridos-effect. ;

The subset of women with low sensitivity according to the old formula will be divided in women with low and high sensitivity according to the new formula. The following analysis will be performed only if the smallest group has  $N \geq 15$ :

- Differences between groups will be analyzed with two-way repeated measures ANOVA: a 2 x (Drug: Placebo *versus* Lybrido) x 2 Group (Low sensitivity new versus high sensitivity new), in which “Drug” is the within-subject factor, and “Group” is the between-subject factor. The dependent variable is the change in number of SSEs between placebo and Lybrido.

The subset of women with high sensitivity according to the old formula will be divided in women with low and high sensitivity according to the new formula. The following analysis will be performed only if the smallest group has  $N \geq 15$ :

- Differences between groups will be analyzed with two-way repeated measures ANOVA: a 2 x (Drug: Placebo *versus* Lybrido) x 2 Group (Low sensitivity new versus High sensitivity new),

in which “Drug” is the within-subject factor, and “Group” is the between-subject factor. The dependent variable is the change in number of SSEs between placebo and Lybrido.

- To evaluate the quality of performance of the renewed demarcation formula for the identification of the Lybrido and Lybridos respondents, a receiver operating characteristic (ROC) curves analysis will be performed. For the true status of the women a classification of women into low sexual attention versus high sexual attention will be made based on the Lybrido- and Lybridos-effect variables: when the score on the Lybrido-effect variable is higher than the score on the Lybridos-effect variable, a women is classified as having low sensitivity for sexual cues and vice versa. For the predicted status of the women the present demarcation formula is used. By using different cut-off values of the present demarcation formula, a ROC curve is constructed and the AUC is derived.

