#### **2.2.2.1 Primary hypotheses explorative part**

- Women with a low sensitivity (as compared to high sensitive women) for sexual cues - as determined by the renewed demarcation formula - will have a higher number of satisfactory sexual events during treatment with Lybrido as compared with Placebo and Lybridos;
- The other way around, women with a high sensitivity (as compared to low sensitive women) for sexual cues will have a higher number of satisfactory sexual events during treatment with Lybridos as compared with Placebo and Lybrido;

Moreover,

- Women with a low sensitive system for sexual cues as determined with the new demarcation formula, will have a higher number of satisfactory sexual events during treatment with Lybrido in comparison with placebo and Lybridos, than women with a low sensitive system established by the original formula;
- Women with a high sensitive system for sexual cues as determined with the new demarcation formula, will have a higher number of satisfactory sexual events during treatment with Lybridos in comparison with placebo and Lybrido, than women with a high sensitive system established by the original formula.

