##### **3.2.2 Secondary Objectives**

- To identify in an iterative process additional psychometric and biological markers for the demarcation formula in order to increase predictive power for sensitivity to Lybrido or Lybridos in women with female sexual interest/arousal disorder (FSIAD with or without FOD as secondary diagnosis), measured by the number of satisfactory sexual events (in a first set of 75 subjects of the total amount of 150 subjects).
- To evaluate the altered demarcation formula in women with female sexual interest/arousal disorder (FSIAD with or without FOD as secondary diagnosis), measured by the number of satisfactory sexual events (in a second set of 75 subjects).

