#### **4.6 Interim Database Lock**

This study will have one interim database lock. This interim database lock will take place on the first 75 subjects with FSIAD who complete the study. This is done so that on these subjects an altered/improved demarcation formula can be based. The data of the second set of 75 subjects with FSIAD who complete the study will be used to validate this altered demarcation formula.

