### 6.1 Determination of Sample Size

MedCalc software (MedCalc Statistics for Biomedical Research 12.7, Ostend, Belgium) was used for the ROC curve power analysis. Assuming balanced design of 75 cases in the positive group and 75 in the negative group, giving a total of 150 cases, resulted in 90% statistical power to be able to detect a minimum AUC of .650 from the null hypothesis value 0.5 (meaning no discriminating power) with an  $\alpha$ -level of .05. The distribution of subjects among the groups was based on previous studies, in which the demarcation formula reliably allocated around 50% of all subjects (with complete screening data) to either group. In the Lybrido(s) Phase IIb studies (EB82 & EB90), 48% was marked as low sensitive and 52% as having high inhibition. This, combined with the theoretical background of the subdivision of these subjects (discussed earlier in the protocol), justifies these number in the power calculation.

The assumed AUC of .650 means that a randomly selected person from the positive group has a higher self-reported number of satisfying sexual events than that for a randomly selected person from the negative group 65% of the time. This assumption is considered realistic from an earlier study as stated above, where the correlation between the demarcation formula and another similar measurement of satisfaction was .83.

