### **Exploratory analyses**

Summary statistics will be described for the FSDS-R, PGI-I and PBE data.

The level of statistical significance will be set at  $p < 0.05$ , one-sided. Data will be presented as mean  $\pm$  standard error of the mean. All statistical analyses will be conducted using IBM SPSS Statistics for Windows (Version 19.0. Armonk, NY: IBM Corp.).

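### Both planned splits by the new formula test whether it adds information to the old one, not the stated hypothesis that groups defined by the new formula respond better

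*Protocol*

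**What the plan says.** The secondary objective (3.2.2) is to find further markers "in order to increase predictive power for sensitivity to Lybrido or Lybridos". Section 2.2.2.1 turns this into a comparison between formulas: women classed low by the new formula should have more satisfactory sexual events (SSEs) on Lybrido, relative to placebo and Lybridos, "than women with a low sensitive system established by the original formula". A mirror hypothesis covers high-sensitive women and Lybridos.

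The test set is fixed in section 4.6: "The data of the second set of 75 subjects with FSIAD who complete the study will be used to validate this altered demarcation formula". For this set, section 6.3 (Testing of the new demarcation formula analysis) plans:

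- a mixed ANOVA of Lybrido-effect and Lybridos-effect by new-formula group;
- a split of the old-low women: "The subset of women with low sensitivity according to the old formula will be divided in women with low and high sensitivity" by the new formula, comparing the Lybrido-minus-placebo change between the two parts;
- the same split in the old-high women, also on Lybrido minus placebo;
- a ROC analysis of the renewed formula.

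Each split is run only if its smaller group has at least 15 women. Significance is one-sided at 0.05.

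**The concern.** The hypothesis compares two overlapping groups. Women whom both formulas call low belong to both, so they cannot separate the formulas. At similar group sizes, the answer rests on the women classified differently: old-high/new-low against old-low/new-high. The first split contains only the second of these groups, and the second split only the first. Together the splits cover all four combinations, but neither sets the two discordant groups against each other.

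The null of each split is that the new label carries no information within one old class. Any new formula with some independent information makes that null false, even if it predicts no better than the old one, or worse. The remaining analyses measure the new formula against no discrimination. The old formula's ROC belongs to the primary validation in all 150 women, including the 75 used to build the new formula, so setting the two AUCs side by side would not compare them in the same women. At stake is whether the secondary objective gets an answer to its own question.

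**Working it through.** **The plan's own figure.** Section 6.1 states: "Assuming balanced design of 75 cases in the positive group and 75 in the negative group, giving a total of 150 cases", which "resulted in 90% statistical power to be able to detect a minimum AUC of .650 from the null hypothesis value 0.5". With Hanley-McNeil standard errors of 0.0473 (AUC 0.5) and 0.0447 (AUC 0.65), two-sided power is Φ((0.15 − 1.96 × 0.0473)/0.0447) = Φ(1.28) = 90%. The figure reproduces (one-sided: 94.7%). The protocol gives no power for the comparison of formulas.

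**The two contrasts.** Let q be the share of women on whom the formulas disagree. Assume each formula calls half the women low. Write LL, LH, HL for old class then new class, and m for the mean drug effect.

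- Mean of new-low women: (1 − q)·m(LL) + q·m(HL)
- Mean of old-low women: (1 − q)·m(LL) + q·m(LH)
- Hypothesis (difference): q·[m(HL) − m(LH)]
- Old-low split: m(LL) − m(LH)

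These are different quantities.

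**Additive illustration (assumed).** Let the effect be b·(wO·old-low + wN·new-low), with SD 1. The split estimates b·wN. The hypothesis concerns q·b·(wN − wO). With equal weights the second is zero and the first is positive.

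**Scale (assumed).** AUC .65 corresponds to √2 × Φ⁻¹(.65) = 1.414 × 0.385 = 0.545 SD between old-formula groups. Setting b·(wO + wN·(1 − 2q)) = 0.545 with wO = wN = 1 gives b = 0.545/(2 − 2q): 0.545, 0.454, 0.389 and 0.341 SD at q = 50%, 40%, 30% and 20%.

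**Simulated rejection of the old-low split, formulas equally good** (75 women, one-sided 0.05, split run only if the smaller group has at least 15):

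| Disagreement | Split is run | Significant if run | Significant, all trials |
|---|---|---|---|
| 50% | about 76% | 49% | 37% |
| 40% | about 54% | 42% | 23% |
| 30% | about 14% | 37% | 5% |
| 20% | 0.7% | – | 0.1% |

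Repeated runs gave 49–52%, 40–42% and 32–37% in the third column; the 30% row is least precise because few trials qualify. The contrast of the discordant groups rejected in about 5%, as it should.

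**New formula worse (50% disagreement).** With wN = 0.7, the split estimates 0.7 × 0.545 = +0.38 SD, while the hypothesis difference is 0.5 × 0.545 × (−0.3) = −0.08 SD. With wN = 0.5 the values are +0.27 and −0.14 SD. The split still favours the new formula in about 31–32% and 20–21% of trials in which it is run. With an uninformative new formula it rejects at about 5%, so it is a valid test of added information.

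**A second model.** Let each formula identify a true class with a given accuracy and independent errors, with d the effect in truly low women. At accuracies 0.75 and 0.75, the share truly low is 0.75²/(0.75² + 0.25²) = 0.90 in LL and 0.50 in LH: split +0.40d, true difference 0. At old 0.75 and new 0.65 the shares are 0.848 and 0.618: split +0.23d, true difference −0.10d. With d = 1 SD the split, when run, is significant in 31% and 16% of trials.

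**How often the split runs.** In the earlier studies "48% was marked as low sensitive and 52% as having high inhibition", so about 36 old-low and 39 old-high of 75. Reaching 15 in the smaller part needs about 15/39 = 38% to 15/36 = 42% reclassified.

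**The case against.** A reader might infer that a significant split would lead the sponsor to declare the new formula improved, or to adopt it in phase 3. The protocol does not support that. Section 6.3 attaches no decision rule to the splits. Section 2.1.6 says the new variable must be tested in an independent experiment, and section 2.1.5.2 mentions phase 3 without a replacement rule. Section 2.1.6 also counts a more practical formula as a gain, so an equally good but simpler one would be a partial success.

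The disagreement rates are assumptions. A rate of 50% means the formulas are unrelated, which is unlikely for a formula obtained by altering the old one. At 20% the split almost never runs. The larger percentages describe the unfavourable end of the range.

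The mixed ANOVA and ROC are not offered as superiority tests; they repeat for the new formula what is done for the old. The statistical analysis plan, not shown, may add a paired comparison.

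All of this limits how far the consequence can be pressed. It does not remove the mismatch: section 2.2.2.1 states a comparison between formulas, and section 6.3 itself fixes contrasts that do not make it.

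**Conclusion.** The point holds for both splits. As written, section 6.3 has no analysis of the new-versus-old hypotheses in section 2.2.2.1; what it plans tests added information. That follows from the definitions of the groups and needs no assumed numbers.

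The size is illustrative. It rests on an assumed 0.545 SD group difference, an additive effect, balanced classes and assumed disagreement. For equally good formulas, the chance of a significant old-low split over all trials runs from about 37% at 50% disagreement to about 5% at 30% and near zero at 20%. Because this is a secondary objective without a stated decision rule, it should be corrected but does not affect the primary validation.

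**What to change.** In section 6.3, make the new-versus-old test a paired comparison of both formulas in the same second 75 women, for example the AUC difference (new minus old) by DeLong or bootstrap. Alternatively, compare the matched drug effect between old-high/new-low and old-low/new-high women. This addresses section 2.2.2.1 directly, but it is a separate estimand: it contrasts mean drug effects between dichotomised groups, whereas the AUC difference compares continuous scores against responder status. Name one as the test.

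Keep the two splits as descriptive analyses of added information, and state that an AUC above 0.5 for the new formula shows prediction, not improvement. It is best settled before the interim lock, when the new formula is derived.

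The cost is wording in the protocol and statistical analysis plan; no new data are needed. The downside is power. If only the new formula carries signal at AUC .65 and disagreement is 40%, the discordant groups have about 0.4 × 75/2 = 15 women each, and one-sided power is about 42%. A non-significant difference must therefore not be read as equivalence.

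### The old-versus-new formula analysis in high-sensitive women tests Lybrido, so the Lybridos hypothesis has no test, and each such analysis depends on a group size that may not be reached

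*Protocol*

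**What the plan says.** Section 2.2.2.1 of the protocol ends with two hypotheses that set the new formula against the old. For low-sensitive women the expected gain is "during treatment with Lybrido in comparison with placebo and Lybridos, than women with a low sensitive system established by the original formula". For high-sensitive women it is "during treatment with Lybridos in comparison with placebo and Lybrido, than women with a high sensitive system established by the original formula".

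Section 6.3, under the testing of the new formula, places this work in the second half of the data: "This will be validated in the second half of the dataset (validation set or testing set"). It then gives two old-versus-new analyses. The first takes women whom the old formula calls low-sensitive and splits them by the new formula. The second does the same for the other group: "The subset of women with high sensitivity according to the old formula will be divided in women with low and high sensitivity" by the new formula.

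In both, the within-subject factor Drug has the levels placebo and Lybrido, and in both the outcome is worded identically: "The dependent variable is the change in number of SSEs between placebo and Lybrido". Each carries the same condition: "The following analysis will be performed only if the smallest group has" at least 15 women.

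**The concern.** The analysis in old-formula high-sensitive women looks like a copy of the low-sensitive one in which the drug was not changed. The slip stands in both the factor and the outcome, so neither part of the text corrects the other. The hypothesis about Lybridos is one of the exploratory part's own stated primary hypotheses, and the secondary objective (section 3.2.2) is to predict response to either drug better. Followed as written, the plan could say whether the new formula improves on the old for Lybrido only.

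The condition on group size adds to this. It closes an analysis when the two formulas agree in most women of a subset, so the old-versus-new question may go unanswered for Lybrido too.

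**Working it through.** **Hypotheses against analyses**

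| Women | Hypothesis (2.2.2.1) | Analysis (6.3) | Not tested |
|---|---|---|---|
| Low-sensitive | Lybrido against placebo and against Lybridos, new better than old | Placebo versus Lybrido | Lybrido versus Lybridos |
| High-sensitive | Lybridos against placebo and against Lybrido, new better than old | Placebo versus Lybrido | Lybridos versus placebo; Lybridos versus Lybrido |

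**The plan's own figure.** The protocol gives no power or expected group size for the old-versus-new comparison. Its only power figure (section 6.1) is for one formula: 75 + 75 women, AUC 0.65 against 0.5, 90% power. With the Hanley-McNeil variance, the standard error is 0.0473 under the null and 0.0447 at 0.65. At two-sided 0.05, (0.15 - 1.96 × 0.0473)/0.0447 = 1.28, which gives 90%. The figure reproduces but does not bear on this comparison.

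**Inputs for the group-size condition**
- Validation set: 75 women (section 4.6).
- Old-formula split: 48% low, 52% high (section 6.1, from the earlier Phase 2b studies). 75 × 0.48 = 36 and 75 × 0.52 = 39.
- Minimum for the smaller group: 15 (section 6.3).

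**Range in which an analysis can run.** In a subset of n women of whom d are reclassified, both groups reach 15 only if 15 ≤ d ≤ n - 15.
- Old-low, n = 36: d from 15 to 21, that is 15/36 = 41.7% to 21/36 = 58.3%.
- Old-high, n = 39: d from 15 to 24, that is 15/39 = 38.5% to 24/39 = 61.5%.

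For both to run, at least 30/75 = 40% of all validation women must be reclassified. For one alone, 15/75 = 20% overall is enough if all the disagreement falls in that subset.

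**Chance that an analysis runs.** With a true disagreement rate q, taken as equal in both subsets and independent between women, P = Σ C(n,x) q^x (1-q)^(n-x) for x = 15 to n - 15. At least one runs with probability 1 - (1 - P_low)(1 - P_high).

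| q | Old-low (36) | Old-high (39) | Both | At least one |
|---|---|---|---|---|
| 20% | 0.3% | 0.6% | <0.01% | 0.8% |
| 30% | 9.2% | 16.4% | 1.5% | 24% |
| 35% | 25% | 38% | 9.5% | 54% |
| 40% | 47% | 63% | 30% | 81% |
| 50% | 76% | 89% | 68% | 97% |

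**Fewer validation women (assumption; the protocol gives no dropout rate).** With 68 women (33/35) the lower limits rise to 45.5% and 42.9%. With 60 women (29/31) the old-low analysis cannot run, because two groups of 15 need 30, and the old-high one needs 15/31 = 48.4%.

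**Outcome wording.** A change score is one value per woman, so it cannot also vary over a within-subject factor whose two levels form that change. Numerically nothing follows from this. In a 2 × 2 mixed ANOVA on the counts, the Drug × Group interaction compares the mean of (Lybrido - placebo) between the groups, and its F is the square of the two-sample t on the change score.

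**The case against.** Several points can fairly be made for the plan, and most of them limit the concern without removing it.

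Lybridos is not absent from the testing of the new formula. The mixed ANOVA on the Lybrido-effect and Lybridos-effect, and the ROC analysis, use both drugs. This stands, but each assesses one formula at a time, so neither fills the gap.

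A minimum group size is an ordinary safeguard. When the formulas agree in nearly all women, few reclassified women carry information by any method. This stands too, and a paired AUC comparison in 75 women may also be imprecise.

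A reader might infer that the comparison can run only if the formulas disagree in about 40% of all women. The arithmetic does not support that. The 40% is roughly the share needed within a subset, or overall for both analyses.

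A reader might also infer that a formula built on the old one cannot differ that much, so the comparison will almost certainly never be done. The protocol does not support this. It states no expected agreement, section 2.1.5.2 considers replacing the digit ratio and the questionnaire items, and section 2.1.6 allows markers to be substituted. At 40% disagreement or more, at least one analysis would probably run with the full 75 women.

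Finally, the change-score sentence might be read as an invalid model. It is loose wording with no effect on the test.

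The mismatch between sections 2.2.2.1 and 6.3 survives all of this. A fuller description in a separate SAP could add detail, but it would not make these two sections agree.

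**Conclusion.** The point holds in this form. The hypothesis that high-sensitive women as defined by the new formula gain more on Lybridos than those defined by the old has no old-versus-new test, and neither has the Lybrido-versus-Lybridos contrast in either hypothesis. That part rests on the text alone and on no assumed rate.

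The group-size condition is a conditional weakness. The chance that at least one analysis runs goes from about 1% at 20% disagreement to 97% at 50%, and the documents do not say where in that range the trial will lie. The figures assume 75 validation women, the 48/52 split, one disagreement rate for both subsets, and that the condition applies to the validation set, as section 6.3 reads. Applied to all 150 women, the lower limits would be about 20% (15/72 = 20.8% and 15/78 = 19.2%).

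The point concerns the secondary, exploratory objective. The primary validation of the existing formula in 150 women is unaffected.

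**What to change.** These changes should be made before the interim lock on the first 75 women, so that the choice of drug and contrast cannot look data-driven.

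1. In the old-formula high-sensitive subset, add the analysis of placebo versus Lybridos. Keep the Lybrido analysis as secondary: women who move from old-high to new-low belong to the new low-sensitive group, so their Lybrido response bears on the other hypothesis.
2. Add the Lybrido-versus-Lybridos contrast that both hypotheses name.
3. State the outcome as the SSE count where Drug is a factor or, equivalently, test the change score by Group. This is a correction of wording only.
4. As a supplement that does not depend on the group-size condition, report the paired AUC difference (new minus old formula) in all validation-set women, with a 95% confidence interval by DeLong or paired bootstrap. It rests on the between-drug classification used in the ROC analysis, so it does not replace the comparisons with placebo in items 1 and 2.

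The cost is a protocol change and a little more analysis. No further women or data are needed. The AUC interval may be wide with 75 women, and the report should say so.

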## **2.2 Hypotheses**

### **2.2.1 Validation of existing demarcation formula**

In the present study, the existing demarcation formula will be validated. Its predictive power for Lybrido and Lybridos sensitivity will be measured using the subjects number of satisfying sexual events on Lybrido and Lybridos as compared to Placebo in the domestic setting in 150 healthy female subjects with FSIAD.

- Women with a low sensitivity (as compared to high sensitivity) for sexual cues as determined by the present demarcation formula will have a statistically significant higher number of satisfying sexual events in the Lybrido regime as compared to the placebo and Lybridos treatments;
- Women with a high sensitivity (as compared to low sensitivity) for sexual cues as determined by the present demarcation formula, will have a significantly higher number of satisfying sexual events in the Lybridos regime as compared to the placebo and Lybrido regimes.

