#### Primary Endpoint Analyses

- Differences in Lybrido-effect and Lybridos-effect between groups will be analyzed with two-way mixed design ANOVA- with 2 within subjects effect variables (Lybrido-effect *versus*

Lybridos-effect) x 2 between subjects group variables (Low Sexual Attention versus High Sexual Attention. The dependent variables are the effect variables Lybrido-effect and Lybridos-effect. ;

- To evaluate the quality of performance of the present demarcation formula for the identification of the Lybrido and Lybridos respondents, a receiver operating characteristic (ROC) curves analysis will be performed. For the true status of the women a classification of women into low sexual attention versus high sexual attention will be made based on the Lybrido- and Lybridos-effect variables: when the score on the Lybrido-effect variable is higher than the score on the Lybridos-effect variable, a women is classified as having low sensitivity for sexual cues and vice versa. For the predicted status of the women the present demarcation formula is used. By using different cut-off values of the present demarcation formula, a ROC curve is constructed and the AUC is derived.

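### The ROC bullet in the new-formula section contradicts itself: it is introduced as evaluating the renewed formula, but its predictor and cut-offs are those of the existing one

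*Protocol*

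**What the plan says.** The last bullet under Testing of the new demarcation formula analysis (Protocol, section 6.3) gives its purpose as "To evaluate the quality of performance of the renewed demarcation formula for the identification of the Lybrido and Lybridos respondents". It then describes how true status is assigned, by comparing each woman's Lybrido-effect with her Lybridos-effect. The predictor is fixed next: "For the predicted status of the women the present demarcation formula is used". A closing sentence, which sets out how the curve and its area are obtained, names that same formula as the score whose cut-offs are varied: "By using different cut-off values of the present demarcation formula, a ROC curve is constructed and the AUC is derived".

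The section's introductory text says that the improved formula will be validated in the second half of the data "using the same analyses as in the validation of the original demarcation formula". The objective served is the second one in section 3.2.2: "To evaluate the altered demarcation formula in women with female sexual interest/arousal disorder".

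**The concern.** The purpose sentence names one formula, and the two sentences that an analyst would program name another. A ROC curve is defined by the score whose cut-offs are varied, so the choice of score decides which formula's AUC is reported. If the bullet is executed as written, the new-formula section yields a second estimate of the existing formula's AUC, now in the last 75 women, and nothing on how well the renewed formula discriminates. That figure could also be reported under a heading that announces the new formula. The ROC is the only analysis in the section that measures discrimination across cut-offs.

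**Working it through.** The point rests on wording, so the check is to establish what *present* means and whether the renewed formula has a ROC anywhere else.

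**1. Meaning of the label.**

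| Place in the protocol | Term used | Formula meant |
|---|---|---|
| 2.2.1, first hypothesis: "Women with a low sensitivity (as compared to high sensitivity) for sexual cues as determined by the present demarcation formula" | present | existing |
| 6.3, primary ROC: "To evaluate the quality of performance of the present demarcation formula for the identification of the Lybrido and Lybridos respondents" | present (three times in the bullet) | existing |
| 2.2.2, 3.2.2 and 4.6 | altered | new |
| 2.2.2.1 | renewed, new | new |
| 6.3, new-formula ROC, opening sentence | renewed | new |
| 6.3, new-formula ROC, last two sentences | present (twice) | existing, if the label is read consistently |

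Section 2.2.1 is headed as validation of the existing formula, so *present* is not a loose word for whichever formula is under discussion.

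**2. Source of the slip.** The last two sentences of the new-formula bullet match the last two of the primary ROC bullet word for word. The opening sentences differ only in *renewed* against *present*. The likely explanation is that the bullet was copied and only its opening was edited.

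**3. Any other ROC for the renewed formula.** ROC analysis appears in section 6.1 (sample size) and in the two bullets of section 6.3. Section 6.1 does not mention the renewed formula, and the primary bullet uses the existing one. No place names the renewed formula as ROC predictor.

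**4. Whether a stated number depends on this.** The only related figure is the 90% power in section 6.1 for an AUC of 0.650 against 0.5 with 75 + 75 women. It can be checked with the Hanley-McNeil variance:

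Var(A) = [A(1 − A) + (n1 − 1)(q1 − A²) + (n2 − 1)(q2 − A²)] / (n1·n2), with q1 = A/(2 − A) and q2 = 2A²/(1 + A).

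- SE at A = 0.5: 0.0473. SE at A = 0.65: 0.0447.
- Power at two-sided 0.05 = Φ((0.15 − 1.96 × 0.0473) / 0.0447) = 90.0%.

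The plan's figure is reproduced. It concerns all 150 women and does not change with this correction.

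For context only, assume that the second 75 women split about 37/38 on true status. At an AUC of 0.65 the two standard errors are then 0.0671 and 0.0635, and power is about 61% two-sided or 73% one-sided. The protocol promises no power for this ROC. The figures show only that the corrected analysis would be estimated in the smaller set.

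**The case against.** The strongest reply is that nobody would be misled. The bullet opens by naming the renewed formula and stands under a heading about the new formula. The introductory text to that section says the same analyses are to be applied to the improved formula, and sections 2.2.2 and 4.6 say that the second 75 completers serve to test the altered formula. This stands: the intent is clear. A reader might infer that the renewed formula's AUC would never be estimated. The documents support that only for the literal text of the last two sentences.

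A reader might also infer that the secondary objective is left untested. The documents do not support this. The section plans a mixed-design ANOVA for validating the new formula, and two further ANOVAs that split the old low and high groups by the new formula. The hypotheses in section 2.2.2.1 concern numbers of satisfactory sexual events by group and drug, which is what the ANOVAs address; none mentions an AUC. One qualification applies. The two further ANOVAs run only if the smaller group has at least 15 women. If the 48%/52% split in section 6.1 holds in the second set, the old groups have 0.48 × 75 = 36 and 0.52 × 75 = 39 women. The new formula would then have to move at least 15/36 = 42% of the first and 15/39 = 38% of the second. These two analyses may therefore not be run, but the mixed ANOVA carries no such condition.

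Finally, section 6 defers the full description to the SAP, which is not at hand and may name the right formula. That lowers the risk. It does not make the protocol sentence correct, because this is a misstatement and not a detail left open.

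**Conclusion.** The point holds as an internal contradiction in one bullet of section 6.3. Read literally, the bullet produces an AUC for the existing formula in the second 75 women and none for the renewed formula. This rests on reading *present* as the protocol uses it in section 2.2.1 and in the primary ROC.

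The reach is limited to the ROC part of one secondary objective, in the part of the study that the protocol calls exploratory. The primary validation in 150 women, the sample size and the ANOVAs for the new grouping are unaffected. A moderate grade is right: the sentences are operative and should be corrected, but the evident intent and the remaining analyses do not support calling it a failure of the objective.

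**What to change.** In the last two sentences of the ROC bullet under Testing of the new demarcation formula analysis, replace *present* with *renewed*, once for the predictor and once for the cut-offs. Add that this ROC is run in the second set of 75 completers, using the formula derived in the first 75. The SAP should carry the same wording.

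Reporting the existing formula's AUC in the same 75 women would help to compare the two formulas. It is optional: the protocol does not promise it and the correction does not need it.

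The cost is two replaced words and one clarifying clause. No patient, visit, measurement or stated number changes. It is best done before the interim lock on the first 75 completers, so that the predictor for the second set is fixed in writing before the new formula is built.
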